### 3.5. Intervention and Sham Treatments

#### 3.5.1. Experimental Group: Intervention

The intervention comprises the interactive podcast program, “Living with Type 1 Diabetes to Grown-Up,” which includes podcast episodes and interactive voice feedback. The program features 36 episodes, released at a rate of three per week over a 3-month intervention period [65]. Based on pilot testing for optimal duration and speech rate [56], each episode lasts 8–15 min with a word count of 160–220 words per minute. The content incorporates participant recommendations and uses appropriate language, presented lightly and engagingly. The topics and subtopics are detailed in Table 1. In addition to episode ratings and encouraged comments, participants will provide voice feedback aligned with the objectives and content of each unit to enhance practical application. During the first 9 weeks of the intervention, every 3 weeks (at Weeks 3, 6, and 9), participants will select a topic from the podcast episodes they have completed and provide voice feedback based on the PRIDE interactive voice feedback protocol and steps, as detailed in Table 2. The principal investigator will then coordinate expert responses tailored to participants' feedback, delivered in the following weeks 4, 7, and 10. Each participant will engage in three personalized voice feedback interactions over the study period, and all feedback will be thoroughly documented to assess TF through content checking, ensuring accurate implementation and alignment with participant needs. While episodes cannot be downloaded, participants can listen to them again throughout the intervention.

Detailed information on the training of interventionists is contained in File S1. Trained interventionists will follow the standard manual to (1) install the podcast program for the experimental group at enrollment by setting up participant codes and accounts; (2) explain the weekly release of three podcast episodes through dynamic, time-limited QR codes and guide participants through the process of submitting and retrieving voice feedback; (3) demonstrate the steps for inputting, uploading, and downloading voice feedback from the research team, followed by participant practice; (4) provide contact information for administrative support and address any related inquiries; (5) collaborate with participants to discuss and set HbA1c control goals at every data assessment point; and (6) facilitate and ensure treatment receipt and enactment throughout the intervention period (see Section 3.6 for detailed plans).

#### 3.5.2. Active Control Group: Sham Treatment

Our previous study demonstrated that e-books did not have a significant impact on glycemic control (HbA1c: 8.30 ± 1.29 vs. 8.82 ± 2.69, *p* = 0.477), diabetes knowledge (16.59 ± 3.26 vs. 15.42 ± 3.85, *p* = 0.336), self-care behaviors (152.94 ± 13.38 vs. 155.95 ± 14.56, *p* = 0.525), self-management confidence (29.82 ± 4.30 vs. 27.63 ± 5.82, *p* = 0.212), or interpersonal distress (11.00 ± 5.01 vs. 10.53 ± 6.54, *p* = 0.811) after 6 months in our prior trial [57]. Therefore, the active control group will receive the e-book “Transitioning from Adolescence to Early Adulthood: The Ins and Outs of Type 1 Diabetes,” compiled from the Healthcare CEO app collection, as a sham treatment. This title and content indicate its suitability as a minimally active control that is thematically relevant [66, 67]. The topics in the e-book include (1) diabetes knowledge, (2) how to manage your blood sugar, (3) eating and exercising well, (4) healthy interpersonal relationships, (5) parent–child harmony, and (6) you are not alone. Each unit includes recommended readings, such as “Needles” and “My Life Is Not Controlled by Diabetes.” Although parts of the themes are similar, the e-book is simplified to 600–800 words of pure text per unit, lacking T1D patient experience sharing and interactive engagement. Participants in the active control group will not be reminded to read the e-book, no additional interventions or consultations will be provided, and no follow-up calls will be made during the intervention. After the study, participants in the active control group will be offered the opportunity to listen to all podcast episodes and receive the same incentives as the experimental group, if desired. The intervention characteristics of the experimental and active control groups are presented in Table 3.

### 3.6. TF

To ensure the fidelity and accuracy of the intervention process and enhance its effectiveness, this study adheres to the five components outlined by the National Institute of Health Behavior Change Consortium: treatment design, provider training, treatment delivery, treatment receipt, and treatment skills enactment [68]. Furthermore, insights from Saarijärvi et al. [69] on training research assistants and backend data analysis are also incorporated.  Table 4 presents a detailed TF strategy, while File S1 provides the relevant manuals and checklists.

#### 3.6.1. Strategies for Enhancing Treatment Delivery and Receipt

To ensure appropriate treatment delivery and receipt, the trained interventionists will send reminders on Wednesdays if backend data shows that participants have not listened to the episodes. Additionally, 1.5 months postintervention, the assistant will contact participants by phone to check for any issues or difficulties with using the podcast without discussing diabetes care–related information to avoid study interference [57]. After the intervention, the administrator will disable the program link from the backend.

#### 3.6.2. Strategies for Enhancing Participant Involvement

Based on the findings from an earlier study [56], strategies to boost participant engagement will be adopted at the treatment design, delivery, receipt, and enactment stages to include (1) increasing the willingness to engage with the podcast program: (A) tailoring the content to resonate with youth culture and language, based on participants' input. (B) Employing professional visual design for the podcast program cover to captivate participants both visually and audibly. An art designer with expertise in nursing and experience with T1D was enlisted to create an appealing cover for the target age group. (C) Enhancing participant engagement through personalized feedback and voice interaction. (D) Encouraging participants to leave voice messages and ratings after each episode. Following the study, the research team will review the messages and select five participants with the most relevant contributions, awarding them a voucher worth NT$300 each. (2) Offering NT$300 vouchers to participants for each completed questionnaire as a token of appreciation. (3) Establishing HbA1c achievement goals, with the Top 5 participants showing the highest percentage improvement receiving NT$500 vouchers at the study's conclusion as an incentive.

### 3.7. Outcomes

The study utilizes structured questionnaires, accessible via QR code, for data collection. All questionnaires are mandatory and have been validated by experts. The estimated completion time is 15–20 min. A detailed description of the psychometric properties of each questionnaire used in this study is available in File S1.

#### 3.7.1. Basic Information Questionnaire

This questionnaire covers age, gender, body mass index, education, occupation, number of hospitalizations, comorbidities, age of diagnosis, disease duration, daily frequency of blood glucose self-monitoring, specialty follow-up, and number of doctor and specialty changes.

#### 3.7.2. Primary Outcome: Wellbeing—Disease Control Outcomes

Assessed through HbA1c, the percentage of self-monitored blood glucose readings within the 70–180 mg/dL range, the number of hypoglycemic events (blood glucose < 70 mg/dL), and the number of hyperglycemic events (blood glucose > 180 mg/dL) [70] will be noted. HbA1c will be recorded from electronic medical records after blood samples are collected during patient visits. The percentage of self-monitored blood glucose readings within the 70–180 mg/dL range will be calculated using the formula: (number of values within the 70–180 mg/dL range/total number of tests)∗100% [57].

A data downloader at outpatient clinics will be used to retrieve the past 3 months' blood glucose data and reset it to prevent data from overlapping or being overwritten. Subsequently, two data collection assistants will simultaneously review the data manually. If discrepancies arise, the principal investigator will verify the data. Finally, interrater reliability will be assessed using Cohen's Kappa coefficient to ensure consistency in their evaluations [71]. In cases of abnormal blood glucose values, such as hypoglycemia, if the participant follows up with a blood glucose check 15 min after consuming carbohydrates, only the first recorded value (i.e., the pretreatment blood glucose value) will be used for analysis. Commercial blood glucose meters can store 500–1000 data points, and participants typically measure 2–5 times daily. Therefore, based on prior studies, data coverage is not expected to be an issue [57].

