### 2.2. Hypotheses

Based on the prior efficacy of apps and internet-based interventions [18, 19, 21], we hypothesized that participants in the experimental group receiving the interactive podcast program, “Living with Type 1 Diabetes to Grown-Up,” would demonstrate better disease control outcomes, along with improved diabetes knowledge, self-care behaviors, and self-management confidence, compared to those in the active control group. We also hypothesized that emotional distress, interpersonal distress, and family conflict would be lower in the experimental group compared to the active control group.

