## 3. Methods

### 3.1. Study Design

This study is a double-blind, parallel, 1:1 randomized controlled trial (RCT). After enrollment assessments, participants will be randomly assigned to either the experimental group, receiving the interactive podcast program, “Living with Type 1 Diabetes to Grown-Up,” or the active control group, receiving a sham treatment using an ineffective e-book, “Transitioning from Adolescence to Early Adulthood: The Ins and Outs of Type 1 Diabetes” which will be given at enrollment [57]. Both interventions will last for 3 months. Outcome measures will be evaluated at four time points: pre-randomization (T0), immediately postintervention (T1), 3 months post-intervention (T2), and 6 months postintervention (T3). This study has been registered at ClinicalTrials.gov (under identifier NCT06464640).  Figure 2 shows the detailed study process.

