#### 3.3.2. Sample Size Calculation

Few studies have explored podcast-based interventions for chronic diseases or illnesses in adolescents. As podcasting is a technology-based intervention method, results from our prior study of Healthcare CEO App [57] were used for sample size calculation. Effect sizes were calculated using Cohen's *d*. For groups of 19 participants each, the mean HbA1c for the experimental vs control group at 3, 6, and 9 months postintervention was 7.93 ± 1.36 versus 8.69 ± 2.40, 8.30 ± 1.29 versus 8.82 ± 2.69, and 8.24 ± 1.58 versus 8.87 ± 2.72, respectively, yielding an effect size of 0.38, 0.26, and 0.32, respectively.

Using G-Power 3.1.9.4 software, the required sample sizes were calculated for each group across the three time points as 18, 38, and 26 participants, respectively. Assumptions included two groups with four repeated measures, *α* set at 0.05, power at 0.80, and a correlation coefficient of 0.5. No participants withdrew from our prior study [57]. However, considering a conservative dropout rate of 12% based on similar online intervention studies with a 6-month follow-up period [64], the number of participants was increased to 21, 44, and 30 per group. The maximum sample size calculated based on the smallest effect size at T2 was chosen. Therefore, the total sample size will be 88 participants.

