### 3.8. Statistical Analysis

Descriptive statistics such as frequency distribution, percentage, mean, standard deviation, and maximum/minimum scores will be utilized to characterize the subjects' demographics, disease characteristics, outcome variables at enrollment, and podcast usage. The efficacy of the intervention will be assessed using generalized estimating equation (GEE) modeling, which accommodates repeated measurements and deals with missing data effectively, following the intention-to-treat principle.

GEE will evaluate differences in outcome variables between experimental and control groups over time. Linear GEE models will be applied for all the continuous outcomes. The models will include fixed effects for the group (experimental vs. control), time (baseline, postintervention, and 3 and 6 months postintervention), and their interaction. The working correlation structure will be selected based on the quasi-likelihood under the independence model criterion [77]. Statistical significance will be determined at *p* < 0.05. All analyses will be conducted using IBM SPSS 26.0 for Windows.

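### Four unranked primary measures at three follow-ups, with no named primary measure, visit or success rule: error control on the primary claim is undefined and, if any success counts, well above 5%

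*Protocol article*

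**What the plan says.** Section 3.7.2 places four measures under one primary-outcome heading: "Assessed through HbA1c, the percentage of self-monitored blood glucose readings within the 70–180 mg/dL range, the number of hypoglycemic events" "and the number of hyperglycemic events (blood glucose > 180 mg/dL"). They are listed without a hierarchy.

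Section 3.1 sets the follow-ups as "immediately postintervention (T1), 3 months post-intervention (T2), and 6 months postintervention (T3"), and no visit is called primary.

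The hypothesis in Section 2.2 is that the podcast group "would demonstrate better disease control outcomes, along with improved diabetes knowledge, self-care behaviors, and self-management confidence". The disease control outcomes are in the plural, and the text does not say whether one, some or all must improve.

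Section 3.8 fits a GEE model to the outcomes: "The models will include fixed effects for the group (experimental vs. control), time (baseline, postintervention, and 3 and 6 months postintervention), and their interaction". It then says "Statistical significance will be determined at *p* < 0.05". It does not say which model term or contrast decides efficacy.

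Section 3.3.2 uses HbA1c only. It derives a separate sample size from the effect at each of three times, and "The maximum sample size calculated based on the smallest effect size at T2 was chosen".

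**The concern.** Which variable is primary is a protocol decision. Contrast coding and adjustment methods can wait for an analysis plan, but this article makes the primary choice under its own heading and leaves it open in three ways: which measure, which visit, and what counts as success.

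Two things are at stake. First, with four measures and up to three visits each judged at 0.05, a significant result on any of them could be presented as success on disease control. The 5% level then does not apply to that claim.

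Second, the measures can disagree. Three of the four come from the same meter download, and two of those are raw counts. Section 3.7.2 expects participants to test 2–5 times a day, so the counts can change with testing frequency alone. If HbA1c fell while hypoglycemic events rose, the plan would give no answer on whether its hypothesis was met.

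**Working it through.** **1. The plan's own figure.** Section 3.3.2 gives HbA1c effect sizes 0.38, 0.26 and 0.32, α = 0.05, power 0.80, four repeated measures and correlation 0.5. A between-groups repeated-measures F test has noncentrality

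λ = f²·N·m / (1 + (m − 1)ρ).

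With f = 0.26, N = 76 (38 per group), m = 4 and ρ = 0.5, λ = 0.0676 × 76 × 4 / 2.5 = 8.22, and power is 0.81. The same formula gives 18, 38 and 25 per group, against the stated 18, 38 and 26. Dividing the stated numbers by 0.88 for 12% dropout gives 21, 44 and 30, and 2 × 44 = 88. The figure is reproduced, but only with the stated Cohen's d entered as f; that is a separate matter. What matters here is that the test behind the sample size is one overall group comparison on one measure, HbA1c.

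**2. Number of tests.** Section 3.8 allows two readings:
- one overall test per measure: 4 tests
- one group contrast per measure at each follow-up: 4 × 3 = 12 tests

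**3. Independent tests.** The chance of at least one p < 0.05 under the null is 1 − 0.95^k.
- 4 tests: 1 − 0.95⁴ = 18.5%
- 12 tests: 1 − 0.95¹² = 46.0%

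**4. Correlated tests.** These are simulated two-sided z-tests, multivariate normal, 400,000 draws. The correlation between visits is set at 0.5. That is the coefficient in Section 3.3.2, and it is also the correlation between change-from-baseline contrasts under an exchangeable structure. The between-outcome correlation is not in the protocol, so a range is assumed. For the columns on the podcast's side, outcomes are oriented so that positive means benefit, and only significant results in that direction count.

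| Between-outcome correlation | 4 tests, either direction | 4 tests, favouring podcast | 12 tests, either direction | 12 tests, favouring podcast |
|---|---|---|---|---|
| 0 | 18.5% | 9.6% | 41.5% | 22.8% |
| 0.2 | 18.0% | 9.1% | 40.4% | 21.2% |
| 0.5 | 15.5% | 7.7% | 35.5% | 18.0% |
| 0.7 | 13.0% | 6.5% | 30.3% | 15.3% |
| 0.8 | 11.4% | 5.8% | 26.8% | 13.5% |

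The single-test reference is 5% in either direction and 2.5% favouring the podcast. If the between-visit correlation also varies, from 0.3 to 0.8, the 12-test rate in either direction runs from 21% to 44%.

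**5. HbA1c alone at three visits.** At between-visit correlation 0.5 the rate is about 13% (14% if independent). Naming HbA1c without naming a visit or a single overall test is therefore not enough.

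**6. Cost of keeping all four as any-of primaries.** Bonferroni levels are 0.05/4 = 0.0125 and 0.05/12 = 0.0042. On the plan's own sizing inputs (f = 0.26, 38 per group), power falls from 0.81 to 0.62 and 0.47.

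**The case against.** Several points can fairly be made for the plan.

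- **The protocol prescribes neither visit-by-visit tests nor an any-of rule.** A reader might infer that there are 12 primary tests and a 30–40% false-success rate. Section 3.8 names no contrast, and the test that reproduces the sample size is one overall comparison. This stands: the 12-test figure is conditional on visit-wise testing, and both ranges are conditional on any success counting. Section 2.2 could equally mean that all four measures must improve, which would not inflate the error.
- **Either-direction rates overstate false success.** The hypothesis is directional, and about half of the false positives would favour the control group. This stands, and both sets of rates are shown. Section 3.8 does not state sidedness; two-sided testing is assumed here.
- **The correlations between outcomes are assumed.** This stands. Three measures share one data source, which may place them towards the lower rates.
- **HbA1c is implied as the lead measure.** It is listed first and sets the sample size. That helps, but the heading still gives all four measures the same status, and HbA1c alone still has no deciding visit or test.
- **Multiplicity procedures are commonly left to the analysis plan, which is not shown.** This stands as far as the missing adjustment method goes. It does not cover the choice of primary measure, which the protocol does make.

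Two further readings are not supported. Adding the outcomes that Sections 3.7.3–3.7.5 label secondary would raise the error rate, but that does not bear on the primary claim. Nor is T2 the protocol's intended primary visit: sizes were computed at all three times and the largest was taken.

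**Conclusion.** The point holds in conditional form. The defect is an undefined primary claim, not a demonstrated error rate of a given size. The protocol has four primary measures of equal status, three follow-ups, no primary visit or success rule, a flat 0.05, and a sample size built on one of the four.

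If any success counts, the two-sided chance of at least one false significant primary result is about 11–19% with one overall test per measure. With each follow-up tested separately it is about 27–41% (46% if all 12 tests were independent). The shares favouring the podcast are about 6–10% and 13–23%, against 2.5%. The 27–41% figure and its podcast share rest on between-visit correlation 0.5, and all the ranges rest on assumed between-outcome correlations of 0 to 0.8.

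The protocol nowhere claims family-wise control, so no statement in it is contradicted. But its main efficacy claim has no defined test, and conflicting results among the four measures could not be resolved.

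**What to change.** Before data are seen, name HbA1c as the single primary outcome with one prespecified two-sided test at 0.05. Two forms would do:
- the group contrast at one named visit, either T2, whose effect set the sample size, or another visit that the sponsor justifies; or
- one overall group-by-time test.

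Move percent of readings in range, the hypoglycemic and hyperglycemic counts, and HbA1c at other visits to secondary. Either apply a Holm adjustment to them, or report estimates with 95% confidence intervals and make no confirmatory claim.

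The cost is a change of wording in Sections 3.7.2 and 3.8. The Data Availability statement says data collection had not yet occurred at the time of writing. The downside is that the other three measures can no longer carry a primary claim. In return, the primary test keeps its 5% level without the loss of power that splitting alpha over 4 or 12 tests would bring.

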			EP35: We went through it together—Part 2 (summary and sharing of PRIDE interaction records)
			EP36: Key point review and temporary goodbye (reviewing critical points of the related topics)

**Table 2 tab2:** PRIDE voice feedback guidelines.

**Steps of voice feedback**	**1. P: Problem—identify the primary problem**	**2. R: Research—review daily activities**	**3. I: Identify—set specific, achievable health management goals**	**4.D: Develop—develop a goal-achievement plan**	**5. E: Establish—develop a self-reward approach**	**6. Self-reflection on goal achievement status**
The first	After listening to Weeks 1–3, identify one of your most significant difficulties in disease understanding, blood glucose management, exercise, and diet (one primary issue). How does this problem impact your health management? For example, frequent post-exercise hypoglycemia, fear of not waking up, and avoiding exercise lead to poorer blood glucose control.	Reflect on the past 3 weeks and applying program knowledge, such as exercise, is essential to investigate your daily activities and identify the causes of the previous problem. For example, there is no habit of checking blood glucose before and after exercise or not knowing how to replenish carbohydrates during exercise.	Based on Weeks 1–3 of learning, set specific health management goals to address the issue. For example, no postexercise hypoglycemia after regular aerobic exercise for three consecutive weeks exists.	List and apply strategies learned from the program to achieve your goals. For example, monitor exercise type and blood glucose changes before and after, analyze the timing of hypoglycemia, and carry juice for incremental carbohydrate intake.	Establish a reward for achieving your goal. For example, if I avoid post-exercise hypoglycemia for 3 weeks, I will treat myself to a healthy meal.	Did you achieve your goal? Reasons for success or failure?

Self-verification (check and upload)						

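### Hypo- and hyperglycemic event counts are not scaled by the number of glucose tests, so a difference in testing between arms can distort two components of the primary outcome

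*Protocol article*

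**What the plan says.** Section 3.7.2 of the protocol article lists four disease-control measures under the primary outcome: HbA1c, the percentage of self-monitored readings in range, and two counts, "the number of hypoglycemic events (blood glucose < 70 mg/dL), and the number of hyperglycemic events (blood glucose > 180 mg/dL".

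The three meter-based measures come from one source. At each assessment the meter is downloaded to "retrieve the past 3 months' blood glucose data" and then reset. The in-range measure is a ratio, "number of values within the 70–180 mg/dL range/total number of tests)∗100". No denominator is given for the two counts. One rule limits repeat values: after a low reading that is treated and rechecked at 15 minutes, "only the first recorded value (i.e., the pretreatment blood glucose value) will be used for analysis". On testing frequency, the section says that "participants typically measure 2–5 times daily".

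Three other places bear on this:

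- **Sections 2.2 and 3.7.4.** The trial expects better self-care in the podcast arm, and self-monitoring of glucose is one of the seven dimensions of the self-care scale.
- **Table 2 (PRIDE voice feedback guidelines).** The worked example for the first feedback round names as a possible cause of difficulty that "there is no habit of checking blood glucose before and after exercise". It gives as a strategy to "monitor exercise type and blood glucose changes before and after".
- **Section 3.8.** The stated model terms are group, time and their interaction. No exposure or offset term is named. Section 3.7.1 collects testing frequency by questionnaire, but nothing links it to the event counts.

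**The concern.** A count of out-of-range meter readings is the product of two things: how often the participant tests, and what share of tests is out of range. Only the second describes glycemic control. Section 3.7.2 removes the first from the in-range measure by dividing by the number of tests, but leaves it in the two event counts.

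Randomization balances testing frequency at baseline in expectation, and the group-by-time term compares change from baseline. Neither protects against a change in testing that follows randomization. Such a change is plausible here because self-monitoring belongs to a behavior the intervention is meant to improve. If the podcast arm tests more, its event counts rise for a reason unrelated to glycemia, and a gain on a secondary outcome works against part of the primary outcome. If one arm tests less, the counts flatter that arm.

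**Working it through.** **Inputs from the documents.** Testing frequency is 2–5 per day and the window is 3 months (Section 3.7.2), taken here as 90 days. The same section gives meter storage as 500–1000 values.

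**The plan's own figure.** The section argues that data will not be lost. At most 5 × 90 = 450 readings accrue, which is below 500, so the argument holds when the meter is reset every 3 months. Lost readings are not the issue.

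**Spread in number of readings.** 2 × 90 = 180 and 5 × 90 = 450. The ratio is 450 / 180 = 2.5. Two participants with the same share of readings out of range can therefore differ 2.5-fold in both counts.

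**Effect of a change in testing.** Expected count = tests per day × 90 × share out of range. If testing changes by a ratio r and the share is unchanged, the count changes by r. For the count to stay level, the share must fall by 1 − 1/r.

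| Tests per day | r | Rise in both counts, same glycemia | Fall in share needed to break even |
|---|---|---|---|
| 3 to 4 | 1.33 | 33% | 25% |
| 2 to 3 | 1.50 | 50% | 33% |
| 3 to 5 | 1.67 | 67% | 40% |
| 2 to 5 | 2.50 | 150% | 60% |

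These rows need no assumption about the share of low or high readings. They do assume that the extra tests are as likely to be out of range as the others. They show what a given change would do; they do not predict the change.

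**Whether the sign can reverse.** The documents give no shares, so two assumed sets are shown, with control at 3 tests a day (270 readings) and podcast at 4 (360 readings).

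- Set A. Control, 5% low and 45% high: 270 × 0.05 = 13.5 and 270 × 0.45 = 121.5. Podcast, 4% low and 40% high: 360 × 0.04 = 14.4 and 360 × 0.40 = 144.0. The in-range share improves from 50% to 56%, yet the counts are 7% and 19% higher.
- Set B. Control, 8% low and 50% high: 21.6 and 135.0. Podcast, 7% low and 42% high: 25.2 and 151.2. The in-range share improves from 42% to 51%, yet the counts are 17% and 12% higher.

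**After scaling.** Dividing by total readings returns the shares themselves (5% against 4%, 45% against 40%, and so on), at any testing frequency.

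**The case against.** The strongest reply is that nothing in the protocol says testing will differ between arms. No expected change is stated. The exercise example in Table 2 is an illustration within one of three feedback rounds, for which participants choose their own topic (Section 3.5.1). No episode description in Table 1 names testing frequency. The control e-book also covers managing blood sugar (Section 3.5.2). In the prior app trial, self-care scores at 6 months were 152.94 and 155.95 (p = 0.525), which gives no support for a rise in testing, although a total score does not exclude one. All of this stands. It limits the claim to what can happen and leaves the size open.

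Two further points stand in part. The 3-month window does fix time at risk, so what is missing is a per-test denominator, not every denominator. The 15-minute recheck rule removes one route by which testing inflates the low count, but added routine or exercise checks still enter.

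Three stronger readings are tempting and are not supported:

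- **That better monitoring will make the podcast look worse.** The sign reverses only if the relative rise in testing outweighs the relative fall in out-of-range readings. A false-positive rate for the trial would depend heavily on assumed within-person variation that the documents do not give, so none is quoted.
- **That the counts are assigned to an unsuitable linear model.** Section 3.8 says "Linear GEE models will be applied for all the continuous outcomes". It does not say how counts will be modeled, and that detail may sit in an analysis plan that is not shown.
- **That higher counts would be read as harm.** Section 3.7.2 lists them as disease-control outcomes, and nothing makes them safety endpoints.

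**Conclusion.** The point holds in limited form. As defined in Section 3.7.2, two of the four disease-control measures mix glycemic control with testing frequency, and the stated model terms do not separate them. This is a matter of the stated outcome definition, which the article sets out in full; the in-range measure beside it is already scaled.

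At unchanged glycemia, a move from 3 to 4 tests a day in one arm would raise both of its counts by 33%, and a 25% fall in the out-of-range share would be needed to offset it. This rests on a 90-day window, on testing within the protocol's own 2–5 per day, and on extra tests being as likely to be out of range as existing ones. Whether testing will differ between arms, by how much and in which direction is unknown. HbA1c, on which the sample size rests, does not depend on testing volume, and the in-range percentage is already scaled per test. The change should be made, but the trial's main conclusion does not hang on it.

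**What to change.** Define both measures against the total number of readings in the same download: percentage of readings below 70 mg/dL and percentage above 180 mg/dL. Alternatively, keep the counts and analyze them with a log-link count GEE that has log(total readings) as offset. In either case, report readings per day by arm and visit so that any change in testing is visible, and state whether rechecks dropped under the 15-minute rule also leave the total.

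The cost is one sentence in Section 3.7.2 and one in Section 3.8. No new data are needed, because the total number of tests is already required for the in-range formula. Two limits should be noted. Scaling corrects the volume of testing but not a change in its timing, such as more checks around exercise; the in-range percentage already shares this limit. If percentages are used, the low, in-range and high shares sum to 100%, so the three carry only two separate pieces of information.
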